## Abstract

**Background:**

After a lesion to the central nervous system, many patients suffer from reduced walking capability. In the first rehabilitation phase, repeated walking exercises facilitate muscular strength and stimulate brain plasticity and motor relearning. However, marked limping, an unsteady gait, and poor management of obstacle clearance may persist, which increases a patient’s risk of falling. Gait training with augmented reality has been recommended to improve gait coordination. The objective of this study is to test whether a gait rehabilitation program using augmented reality is superior to a conventional treadmill training program of equivalent intensity.

**Methods/design:**

The GASPAR trial (Gait Adaptation for Stroke Patients with Augmented Reality) is a pragmatic, parallel-arm, single-center, nonblind, superiority randomized control trial in neurorehabilitation. The setting is a rehabilitation clinic in Switzerland. The planned number of participants is 70–100. The intervention uses instrumented treadmills equipped with projectors that display shapes on the walking surface. The principle is that patients must adapt their gait to the image that unfolds in front of them. Specific exercises for gait symmetry, coordination enhancement, and gait agility are provided. The program includes twenty 30-min sessions spanning 4 weeks. The comparator group receives standard treadmill training of a similar frequency and intensity. The main outcome to be measured in the trial is walking speed, which is assessed with the 2-min Walk Test. Moreover, gait parameters are recorded during the gait training sessions. Other outcomes are balance control (Berg Balance Scale) and the fear of falling (Falls Efficacy Scale). The statistical analyses will compare the baseline assessment for each participant (before the intervention) with a post-intervention assessment (taken a few days after the end of the program). Furthermore, a follow-up assessment will take place 3 months after discharge.

**Discussion:**

The study results will provide new knowledge about recovery in neurological patients and will contribute to the design of better rehabilitation programs to accompany this process. The findings will also help health care funders to decide whether treadmills equipped with augmented reality capabilities are a worthwhile investment.

**Trial registration:**

ClinicalTrials.gov ID: NCT02808078, registered on 16 June 2016.

## Background

In high-income countries, strokes are the third leading cause of death after cardiovascular diseases and cancers. In Switzerland, about 16,000 people suffer a stroke each year [1]. However, over the last few decades, the death rate following strokes has continuously declined in developed countries because of improvements in primary care. The corollary to this trend is an increased burden on rehabilitation units because of stroke survivors with severe disabilities [2]. The major long-term disability that hinders stroke survivors in recovering a normal life is partial paralysis affecting the extremities. Six months after a stroke, 50 % of stroke survivors still suffer some degree of hemiparesis and 30 % are unable to walk without assistance [3].

In addition to strokes, other circumstances that damage neural tissue can induce similar disabilities. Traumatic brain injuries (TBI), most commonly induced by falls or road traffic accidents, are also a significant issue in Switzerland, with about 850 severe cases per year [4]. Patients with traumatic spinal cord injuries (SCI), representing about 150 cases per year, can be added to this number [5]. Roughly 50 % of these patients suffer from incomplete injuries and thus exhibit residual locomotor capacities [6].

During the months following an injury to the central nervous system, patients partially recover motor and sensory patterns that were in place before the injury. In stroke patients, the maximum degree of recovery typically occurs within the first 3 months, then it progresses at a slower rate until 6 months have passed [7]. This recovery process is in part driven by brain plasticity. In short, redundant connectivity exists in the brain, and new functional circuits can form via remapping between cortical regions [8, 9]. It has been shown that providing an enriched environment stimulates plasticity and facilitates recovery [9]. Although further studies are needed to better understand brain plasticity in humans [10], neurorehabilitation is largely based on the premise that a set of well-chosen exercises can stimulate neural plasticity and enhance the recovery process.

The following are general guidelines for early neurorehabilitation [11]: (1) care provided by a multidisciplinary team, working together in close cooperation to improve a patient’s independence, (2) task-specific training, in which specific functional tasks are practiced repeatedly, and (3) high-intensity practice. This approach applies to both stroke survivors and TBI patients [12]. It is likely that, in the case of stroke survivors specifically, strength training, overground walking training, and speed-dependent treadmill training can improve aspects of gait [13–16]. To be effective, walking training should occur with an average frequency of 3–5 times weekly, in sessions lasting from 20 to 60 min [15]. Concerning patients with incomplete SCI, strong evidence also exists that repeated walking exercises enhance locomotor recovery [6]. Specifically, task-oriented physiotherapy and manual/robotic treadmill training with bodyweight support have been recommended to stimulate brain plasticity [17].

A favorite target for neurorehabilitation is dynamic and static balance. Patients with gait disorders of neurological etiologies are prone to frequent falls [18–20]. Such falls are induced by altered gait coordination which reduces the patient’s adaptability to environmental demands. A major cause of coordination deficit is asymmetry in the propulsive forces between limbs. Altered proprioception [21], gait ataxia, and vestibular disorders [22] may also induce coordination issues. Balance control can also be compromised because of poor central integration of sensory inputs [23]. Although classical interventions have been shown to improve walking speed [16], asymmetric gait patterns and poor coordination may persist [24]. Different approaches have been proposed to improve gait coordination in these patients, such as task-specific walking practice, ankle-foot orthoses, and functional electrical stimulation [25]. Meta-analyses have shown that the best method for training gait coordination in stroke patients is auditory cueing [13, 25]. In this therapy, patients must synchronize their steps with rhythmic auditory stimuli given at a pace that corrects temporal asymmetries of the gait pattern. A recent systematic review has shown that the addition of 30 min of cueing cadence to gait training, four times a week for 4 weeks, is likely to improve the walking ability of stroke patients [26].

In the last decade, the use of visual cues in interventions aimed at improving gait coordination has been proposed. In a manner similar to auditory cueing, the intent of these visual cues is to encourage patients to walk with a more symmetrical gait pattern. The use of augmented reality (AR), i.e., the projection of shapes over the walking surface of treadmills, can also serve to exercise gait agility. It has been proposed that gait adaptability can be increased through a specific program in which visual cues are projected to trigger step adjustments (e.g., target stepping, obstacle avoidance) [27]. Preliminary results in a limited number of chronic stroke patients have shown that visually-guided gait training improved walking speed, balance, and the level of physical activity [27]. The underlying neurophysiological mechanisms for such improvement may be that this type of program allows for better exploitation of alternate sensory modalities to provide feedback regarding the ongoing movement. In addition, it cannot be excluded that stimulating the brain with an enriched visual environment related to the trained task stimulates neural plasticity. Finally, offering a variety of gait exercises may increase a patient’s motivation. Despite these promising findings, the lack of large clinical trials to date prevents us from drawing definitive conclusions about the usefulness of visually-guided stepping for gait rehabilitation.

### Trial objectives

The main goal of the GASPAR (Gait Adaptation for Stroke Patients with Augmented Reality) trial is to assess the efficacy of a treadmill training program that uses visually-guided stepping (AR) during the first phase of rehabilitation for patients with neurological gait disorders following a stroke. In addition, by the use of a pragmatic design, we seek to increase the generalizability and applicability of the study’s potential findings [28]. Consequently, in order to reflect the typical population in a neurorehabilitation center, we include patients with gait disorders of different etiologies; i.e., in addition to stroke patients, the study includes SCI and TBI patients who need gait rehabilitation. The AR program aims at three therapeutic goals: (1) to improve walking speed, which is important to ensure the independence of the patients in their daily lives, (2) to correct gait asymmetry, which may lead to their recovery of a more functional and physiological gait, thus improving gait coordination and reducing their risk of falls, and (3) to exercise gait agility, which may enhance patients’ adaptability to environmental changes while walking and hence again reduce fall risks. We also focus on assessment of the efficiency of the AR intervention. Specifically, we seek to document the patients’ adherence to, and compliance with, the program and to assess their tolerance for AR walking.

## Methods/design

### Trial design

The GASPAR trial is a pragmatic, parallel-arm, single-center, nonblind, superiority randomized control trial in neurorehabilitation. The main objective is to test whether a 4-week gait rehabilitation program that uses AR is superior to a conventional treadmill training program of equivalent intensity. The participants’ flow is shown in Fig. 1, and the Standard Protocol Items: Recommendations for Interventional Trials (SPIRIT) schedule [29] is given in Table 1. Baseline assessments (T0) are taken prior to allocation, which consists of blocking randomization (2:1 ratio) with stratification according to disease etiology. Post-intervention assessments of the two groups (T1) serve to compare the short-term efficacy of the different interventions. Three months after discharge, follow-up assessments (T2) take place to detect potential long-term effects.

**Fig. 1 Fig1:**
[figure not shown]
Flowchart of the Gait Adaptation for Stroke Patients with Augmented Reality (GASPAR) trial

**Table 1 Tab1:** Schedule of enrollment, interventions, and assessments according to the SPIRIT guideline

Study periods	Screening	Baseline assessment (T0)	Treatment, intervention period				Post-intervention assessment (T1)	Follow-up (T2)
Time (week)	−3 to −1	0	1	2	3	4	5	15 w after discharge
Patient information and informed consent	x							
Demographics	x							
Medical history	x							
Inclusion/exclusion criteria	x							
Allocation (after T0)		x						
Gait training (Intervention)			x	x	x	x		
Walking speed (2-min Walk Test)		x					x	
Balance (BBS)		x					x	
Gait parameters			x	x	x	x		
Compliance and motivation (questionnaire)				x		x		
Fear of falling (FES)							x	x
Falls Diary								x
Quality of life SF-36								x
Concomitant therapy (usual care for inpatients)	x	x	x	x	x	x	x	
Adverse events		x	x	x	x	x	x	

*BBS* Berg Balance Scale, *FES* Falls Efficacy Scale, *SF-36* Short Form 36-item questionnaire, *w* week

### Setting

The study takes place in the Clinique Romande de Réadaptation (CRR, Sion, Switzerland). This clinic offers 145 beds and is one of the main rehabilitation centers in western Switzerland (with its 2.1 million inhabitants). Because of its affiliation with the accident insurance company SUVA, the CRR is a common referral center for traumatic injuries, especially for SCIs. The overall objective of the CRR’s therapeutic program is to take care of patients through a multidisciplinary approach to improve their quality of life, functional status, and chance of returning to work. The number of hospitalized patients at the CRR is about 1200 per year, with an average stay of 40 days. Recruitment for this study began in June 2016. A 2-year framework is planned for the study, with possible adjustments according to the results of the interim analyses (see below).

### Participants

Study participants will be recruited from among the inpatients admitted for neurorehabilitation at the CRR. Selection of the inclusion criteria was guided by the rationale of reflecting the prevailing choice in neurorehabilitation clinics of specific therapies that are tailored to patients’ needs. A summary of the inclusion/exclusion criteria is shown in Table 2. Potential candidates will be monitored during their first 3 weeks after admission (Fig. 1). Motor functions will be assessed by a skilled neurologist, who will evaluate the need for gait rehabilitation. If and when the candidate is able to walk during a 2-min test, a final decision for inclusion will be made. Those candidates who do not exhibit sufficient walking capacities after 3 weeks will be excluded.

**Table 2 Tab2:** Inclusion and exclusion criteria

Inclusion criteria	Exclusion criteria
Patient with stroke, traumatic brain injury, or spinal cord injury in acute to subacute phase	Age <18 years
First stage of rehabilitation (<40 days after incident)	Clinically significant concomitant disease states (e.g., cardiovascular disease) that may threaten the patient’s health in case of sustained exercise
Need for gait rehabilitation because of at least one of the following conditions: • Paresis of the lower extremities • Severe balance disorders • No walking at admission	Concomitant gait disorders induced by acute to subacute musculoskeletal injuries (e.g., fracture of the lower extremities)
Ability to walk for 2 min without aid or with minimal aid, namely: • With the help of one person, or: • With walking aid (cane, walker)	Severe preexistent gait disorders that deeply affect walking abilities and gait pattern, either because of musculoskeletal (e.g., severe osteoarthritis) or neurological (e.g., Parkinson’s disease) etiologies
Informed consent as documented by signature	Severe noncorrected visual impairment.
	Inability to follow the procedures of the study, e.g., because of language problems, psychological disorders, dementia, etc.

### Assignment of interventions and blinding

Assignment is effected by a block randomization procedure with varying block size, implemented by independent researchers not affiliated with the GASPAR study. The STATA package RALLOC [30] is used to generate the sequences. The ratio between the intervention and the control group is 2:1; this facilitates recruitment [31] and provides a broader range of information and experience about the AR program. In addition, stratification is made according to the type of injury: stroke patients, TBI patients, and SCI patients. This procedure ensures the comparator and treatment groups to be populated by patients with comparable disease etiologies and thus facilitates interpretation of the results. Sequentially numbered, opaque, sealed envelopes are used to conceal the allocation. Informed consent is obtained by the principal investigator or his/her delegate. Inclusion is confirmed by the referring neurologist. After baseline assessments are taken (T0), the sealed envelope is opened to allocate the participant.

Given the nature of the intervention and its clinical setting, masking is not possible. However, the use of an objective measure as the primary outcome minimizes the risk of bias.

### Medical devices

The intervention uses two different treadmills:The FDM-T treadmill (Zebris Medical, Isny im Allgäu, Germany): this treadmill is equipped with a grid of 10,000 capacitive sensors aimed at analyzing foot pressure (200-Hz sampling rate). The walking surface is 170 × 65 cm. Handrails and a harness ensure optimal safety even for frail individuals. A wide-angle projector (beamer) situated in front of the belt projects stepping targets for the purpose of visual gait training. The Zebris treadmill has been successfully used for gait rehabilitation in patients with Parkinson’s disease [32]The C-Mill treadmill: this treadmill (MotekForce Link, Doorn, The Netherlands) is equipped with an embedded 70 × 300 cm vertical force platform. The long walking surface allows users to exercise gait agility in varying positions along the belt. The treadmill records the vertical force and the position of the center of pressure at a sampling rate of 500 Hz. A projection system displays visual objects on the walking area from the right side of the treadmill. Three recent studies have highlighted the potential of the C-Mill treadmill for stroke rehabilitation [27, 33, 34]

### Intervention

The intervention consists of 20 gait training sessions over 4 weeks. Each training session lasts 30 min. The first 10 sessions (2 weeks) use the Zebris treadmill for basic training of walking speed, step length, and gait symmetry. In the last 2 weeks (10 sessions), the C-Mill treadmill is used for training that is more oriented toward gait agility:Zebris sessions: the gait training performed on the Zebris treadmill aims at improving walking speed, step length, and gait symmetry. The 30-min session begins with a 1-min warmup used to record gait parameters. Then, 5 × 5-min walking intervals are proposed to the participant, punctuated by breaks of 30 s to 1 min. In the first interval, the patient must simply synchronize his/her steps with visual targets (“stepping stones”) based on the gait parameters recorded during the warmup. Then, two types of training are proposed according to the patient’s needs: (1) symmetry training, where the stepping stones are progressively adapted toward a more symmetrical pattern, and (2) step-length training, in which the stepping stones are progressively adapted to present longer steps to the participant. Finally, a 1-min walk without stepping stones is performed at the end of the session to evaluate the immediate effect of the session on the patient’s gait parametersC-Mill sessions: C-Mill sessions aim at training gait agility, that is, speed adaptation and obstacle avoidance. Similar to the Zebris session, the 30-min C-Mill session is divided into 5 × 5-min walking intervals, preceded by a 1-min warmup and followed by a 1-min final assessment. The first interval is dedicated to symmetry or step-length training; the stepping stones are adjusted to provide asymmetry correction or longer steps. In the second interval, the participant must continuously adjust his/her steps to random variations in the position of the stepping stones (varying step length). During the third interval, the patient follows a target area that moves back and forth over the entire length of the treadmill, requiring coordinated speeding up and slowing down. The fourth interval is similar, but with increased difficulty (higher acceleration). Finally, training that includes obstacle avoidance is proposed: unilateral and bilateral obstacles are projected in front of the participant, who must step over them. The speed at which the intervals are performed is kept constant throughout one session, but is progressively increased from one session to another.

The intervention is tailored to the needs and capacity of each participant. For instance, fatigue might make it impossible for a patient to walk for the targeted 25 min, or a frail patient might not make sufficient progress to use the C-Mill after 2 weeks on the Zebris treadmill. Conversely, higher-functioning patients might benefit from C-Mill treatment earlier. The number of intervals performed in each session and the exact training program are documented and taken into account in the statistical analysis.

### Comparator

The choice of intervention for the comparator group reflects a balance between the ethical obligation to provide efficient therapy to all participants and the requirement of standardization to specifically assess the efficacy of AR gait training. Therefore, we exercise participants in the comparator group with the same treadmills and with comparable frequency and intensity to the participants in the intervention group, but without the AR. The walking exercises consist of a progressive speed increase within and between the sessions.

### Concomitant treatments

The interventions are fully integrated into the CRR’s therapeutic program, which includes individual and group therapies (exercises, joint mobilization, speech rehabilitation, etc.) every weekday for a mean time of 2.5 h. The participants in the study follow the usual schedule of care, except that some of the routine physiotherapy sessions are replaced by the study interventions.

### Study outcomes

The selection of the outcomes was guided by three criteria: (1) importance for the patient, (2) ease of implementation in a clinical context, and (3) validity to assess the recovery of locomotor function and gait coordination. A summary of the selected outcomes and their specific aims is presented in Table 3. The principal outcome is walking speed, which is a widely used index in research and in rehabilitation clinics [16]. Furthermore, speed is a good predictor for a patient’s independence during daily life activities [7, 15]. As additional indexes of walking ability, we collect gait data during every training session, taking advantage of the embedded sensors in the treadmills. Typical spatiotemporal parameters are measured: step length, step width, step time, stance phase duration (percentage of gait cycle), and swing phase duration (percentage of gait cycle). Moreover, spatial and temporal left/right asymmetries and stride-to-stride variability are assessed. Recording gait parameters on a daily basis will allow for detailed analysis of the participants’ evolution during the intervention. Other outcomes are related to balance and fall risk, such as the Berg Balance Scale (BBS), a falls efficacy questionnaire (FES), and a Falls Diary after discharge. The assessments (T0, T1) are performed by skilled therapists as part of usual care. Finally, the patients’ subjective perceptions of the intervention and their quality of life at home 3–4 months after discharge are also investigated. Data management follows the clinical practices recommended by the ISO:14155 standard.

**Table 3 Tab3:** Trial outcomes

Outcomes	Assessments	Objectives
Walking speed	2-min Walk Test [36]	To estimate the overall effect of intervention on walking abilities
Gait parameters	Spatiotemporal parameters (including symmetry) measured by the instrumented treadmills	To measure participant’s gait in each training session for analyzing longitudinally the evolution of walking abilities
Balance	Berg Balance Scale (BBS) [37]	To estimate the effect of intervention on static balance
Fear of falling	Questionnaire: adapted Falls Efficacy Scale (FES) [38]	To assess the participant’s confidence in performing daily living activities that require balance control
Falls	Falls Diary completed by the participant over the 3–4 months following discharge	To measure effective fall rate at home
Perception of the intervention	Ad-hoc questionnaire (tailor-made survey)	To evaluate the patient’s subjective perception of the intervention
Quality of life	Questionnaire: Short Form 36-item (SF-36) questionnaire [39]	To obtain an overall survey of wellbeing and quality of life

### Sample size

An interim analysis based on 30 participants with complete data will be conducted to perform a power analysis and to compute the final sample size. The current estimation (as of June 2016) is that a total of 70 to 100 participants will be recruited. The reasons for such an approach are as follows: the hospitalization statistics for the years 2014 and 2015 show that about 300 patients per year were admitted for neurorehabilitation at the CRR, of which 70 were acute to subacute patients. Retrospective analyses of medical files over recent years indicate that 35–50 patients per year would have been eligible for the study: 20–25 stroke patients, 10–15 TBI patients, and 5–10 SCI patients. As a result, approximately 70–100 eligible candidates are expected over the 2-year framework of the study. The uncertainty of this number results from the substantial year-to-year variability seen in patients’ profiles. A preliminary power analysis is not possible for two reasons: (1) the data currently available in the literature about walking speed in acute to subacute TBI and SCI patients are sparse and inconsistent, and (2) while more studies report changes in walking speeds in stroke patients [35], a substantial heterogeneity exists concerning the time of measurement and inclusion criteria for these studies. As a result, we do not have yet sufficient information to estimate the variance of our principal outcome. Consequently, we plan to assess the variance of the outcomes and the effect sizes with an interim analysis based on 30 subjects. The definitive sample size will be assessed accordingly.

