### Statistical analysis

Statistical analyses will be supervised by a skilled statistician and performed with MATLAB and STATA. We will analyze all randomized participants for whom the T1 assessment of the primary outcome and at least one training session are available (i.e., the “intention-to-treat” principle). The interim analysis, including 30 participants, will guide the final statistical methodology. The short-term efficacy of the intervention will be analyzed using the changes between T1 and T0. As the null hypothesis, we postulate that the change before and after the intervention (T1–T0) will not differ between the two groups. We will use simple comparison tests (*t* tests) and multiple regressions; in this case, intervention intensity (number of training sessions), disease etiology, and age will be used as covariates. Furthermore, we will longitudinally analyze (linear growth model) the gait parameters recorded in each gait training session; we hypothesize (H0) that the change over time will be equivalent between groups. We will also assess the difference between groups for the outcomes that are measured at T2 (3-month follow-up). Finally, as a subgroup analysis, we plan to analyze stroke survivors, TBI, and SCI patients separately.

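### The 30-participant interim uses observed effect sizes to set the final sample size and also guides the final method: the effect is too noisy to size the trial, and type I error is left unprotected to a degree that depends on an unstated rule

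*Protocol article*

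**What the plan says.** The Sample size section explains that no power analysis is possible yet and ends its reasoning on the lack of information about the variance of the principal outcome. It then commits to an interim: "An interim analysis based on 30 participants with complete data will be conducted to perform a power analysis and to compute the final sample size". What will be estimated goes beyond the variance: "we plan to assess the variance of the outcomes and the effect sizes with an interim analysis based on 30 subjects". The consequence follows directly: "The definitive sample size will be assessed accordingly". The only total given meanwhile is that "a total of 70 to 100 participants will be recruited", described as a current estimation and derived from expected eligible admissions over two years.

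The Statistical analysis section gives the interim a second job: "The interim analysis, including 30 participants, will guide the final statistical methodology". It lists t tests on the T1–T0 change and multiple regressions with number of sessions, etiology and age as covariates. The analysis set is every randomised participant with a T1 primary outcome and at least one session, so the interim patients are included. The null hypothesis is that the change does not differ between groups.

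The Setting section makes the two-year framework adjustable as well, "with possible adjustments according to the results of the interim analyses". The Assignment section states that "The ratio between the intervention and the control group is 2:1" and that "Given the nature of the intervention and its clinical setting, masking is not possible".

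**The concern.** The gap the protocol sets out to fill is the unknown variance. A variance can be estimated without comparing the arms. Adding effect sizes lets the observed treatment difference decide how many more patients enter the same test, and the same look may also shape which test that is. Two things are at stake.

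- **The sample size itself.** An effect estimated on about 30 patients is very imprecise, so the resulting total may be far from what the trial needs. The 70–100 forecast is not a power calculation, so nothing else supports the final number.
- **The false-positive rate.** If the total or the method depends on the observed effect and the final test is read at the nominal level, type I error can exceed 5%.

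The word between-group does not appear beside effect sizes in the article. It is an inference, because a power analysis for the stated null hypothesis needs the between-group effect.

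**Working it through.** **Inputs from the article:** interim at 30 participants; 2:1 allocation, so about 20 against 10; provisional total 70–100; 35–50 eligible patients per year for 2 years; t test and covariate regression on the T1–T0 change. **Assumed, because the article gives none:** two-sided alpha 0.05, 80% power, and true effects of 0.3, 0.5 and 0.8 SD.

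**1. The stated total.** 2 × 35 = 70 and 2 × 50 = 100 (strata 20 + 10 + 5 = 35 and 25 + 15 + 10 = 50). The figure reproduces as a recruitment forecast. At 2:1 the total needed for an effect d (in SD units) is N = 4.5 × (1.960 + 0.842)² / d² = 35.3 / d². The detectable effect is therefore √(35.3/70) = 0.71 SD at N = 70 and √(35.3/100) = 0.59 SD at N = 100. Power at 0.5 SD is 50% and 65% respectively.

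**2. Precision of the interim effect.** SE = √(1/20 + 1/10) = 0.387 SD. The 95% half-width is 0.79 SD (t, 28 df). The middle half of estimates lies within 0.674 × 0.387 = 0.261 SD of the truth. Totals below are rounded up to whole 2:1 blocks.

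| True effect (assumed) | N needed | Middle half of interim estimates | N implied | Wrong sign |
|---|---|---|---|---|
| 0.3 SD | 393 | 0.04 to 0.56 | over 20,000 down to 114 | 22% |
| 0.5 SD | 144 (141 unrounded) | 0.24 to 0.76 | 621 down to 63 | 10% |
| 0.8 SD | 57 | 0.54 to 1.06 | 123 down to 33 | 2% |

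This step needs no assumption about the decision rule.

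**3. Type I error from re-sizing.** Simulation under the null, 400,000 trials per rule. At 30 patients the total is reset for 80% power at the observed effect, then an unadjusted 5% t test is run on all patients. Two variants: N set from the absolute effect, or N sent to the maximum when the estimate is negative.

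| Range allowed for N | Absolute effect | Negative sends N to maximum |
|---|---|---|
| fixed at 99 (check) | 0.050 | 0.050 |
| 69–99 | 0.055 | 0.053 |
| 30–99 | 0.068 | 0.059 |
| 30–300 | 0.079 | 0.064 |
| essentially uncapped | 0.083 | 0.067 |

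The worst case over any rule that keeps N within 70–100 is 0.056 (numerical integral of the conditional error).

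**4. Type I error from choosing the method.** If the t test or the regression is kept according to the smaller interim p value, with N fixed at 99, the rate is 0.056 to 0.064 (12,000 trials each, assumed covariate R² 0.2 and 0.4, Monte Carlo SE about 0.002). With re-sizing inside 70–100 added, a separate simulation of 8,000 trials gave 0.065.

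**5. The alternative.** If N is reset from the pooled within-group SD only, against a fixed difference (0.6 SD as an illustration), type I error is about 0.051–0.053. The SD is not precise either: its 95% limits at 28 df are 0.79 to 1.35 times the estimate. A nominal N of 99 could then be 99 × 0.794² = 62 to 99 × 1.352² = 181.

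**The case against.** The strongest reply is that the inflation is small on the trial's own numbers. Within 70–100, re-sizing costs about half a percentage point, and the article provides neither for ending at 30 nor for declaring success there. This largely stands. Its limit is that 70–100 is a current estimation from admissions, not a floor or a cap, and the purpose of the interim is to replace it.

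Second, the article says t tests and regressions will both be used. It does not say that the interim picks one, still less by p value. This stands too: the 5.6–6.5% shows what an unrestricted choice could do, not a rule in the plan.

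Third, no adjustment being stated is silence, and alpha handling may sit in a fuller document that is not shown. That is fair, so the point does not claim that the final test will be unadjusted. It does not remove the concern, because the article itself says that effect sizes set the sample size and that the interim guides the methodology.

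Fourth, sizing from the SD is also loose at 30 patients. That is true, as step 5 shows, and it is a cost of the remedy.

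A reader might also infer that the interim is an early efficacy test, that type I error is near 9–10%, or that knowledge of the interim result will bias later assessments. The documents do not support these. No efficacy stopping is stated. Rates that high need a trial that may end at 30 under an unfavourable rule, or analyses the article does not list. In a nonblind trial the staff already know the allocation, and the article relies on an objective primary outcome; nothing says how interim results will be shared.

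**Conclusion.** The point holds as a design choice that should be fixed. The firm part is precision: with an SE of 0.39 SD, the observed effect at 30 patients cannot size this trial at any of the assumed true effects. The type I part is real but conditional on a rule the article does not give: about 5.3–5.6% from re-sizing within 70–100, about 6–8% if the total may fall to 30 or rise well above 100, and about 5.6–6.5% if interim p values select between the two listed analyses. These rates assume a final test at an unadjusted two-sided 5%, and the totals assume 80% power. They also rest on reading effect sizes as between-group, which the stated null hypothesis makes the natural reading.

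**What to change.** Change the wording in three sections.

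- **Sample size:** at 30 participants estimate only the pooled SD of the primary outcome and the T0–T1 correlation. Combine these with a walking-speed difference fixed in advance as the smallest worth detecting. Compute no effect by arm.
- **Statistical analysis:** replace the sentence that lets the interim guide the methodology with one primary model, fixed before the interim.
- **Setting:** tie any adjustment of the two-year framework to the re-estimated sample size, not to interim results in general.

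If the arm effect must be used, pre-specify a combination test or another form of alpha control.

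The cost is wording, plus the need to name a target difference now. The re-estimated total will still be uncertain, because the SD is imprecise at 30 (a nominal 99 could be about 62 to 181).
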